## **8.3 Statistical methods**

### **8.3.1 Analysis Populations**

(1) The number of enrolled patients and the number of patients who complete the trial in each center are listed to generate three analysis datasets (mITT, PPS, and SS).

(2) The patients who drop out and are excluded are listed, along with the reasons.

### **8.3.2 Demographic and baseline Characteristics**

Demographic and baseline characteristic values were summarized using descriptive statistics:

(1) The number of cases, mean, standard deviation, median, and interquartile range (IQR), are calculated for continuous variables. Use means and standard deviations (SDs) for normally distributed data and medians and interquartile range (IQR) for data that are not normally distributed.

(2) The frequency and percentages are calculated for the categorical variables.

(3) The inferential statistical results (P values) are given as descriptive results.

### 8.3.3 Outcome analysis

- **Analysis of primary outcome measures**

The DFS is calculated using the Kaplan-Meier method after the last participant has been enrolled for three years. The median DFS time and its 95% confidence interval are compared between the two groups using the log-rank test. Cox regression is used to calculate the hazard ratio and its one-sided 95% confidence interval between the two groups. According to the prespecified noninferiority criteria, the inferiority of the treatment to be tested compared with the control treatment is determined.

- **Analysis of secondary outcome and other pre-specified outcome measures**

(1) Pathologic outcomes, including the TME quality, negative CRM, and negative DRM, are presented as numbers (percentage) and compared using the Chi-square test.

(2) The operation time (min) and estimated blood loss (ml) are compared between the groups by the Wilcoxon method.

(3) The OS is calculated using the Kaplan-Meier method after the last participant has been enrolled for three years. The median OS time and its 95% confidence interval are compared between the two groups using the log-rank test.

(4) The OS when the last participant is enrolled for five years is determined by using the Kaplan-Meier method. The median OS time and its 95% confidence interval are compared between the two groups using the log-rank test.

(5) Time to tumor recurrence is determined using the Kaplan-Meier method. The median time of recurrence and its 95% confidence interval are compared between the two groups using the log-rank test.

(6) The perioperative recovery time is compared between the groups using the Wilcoxon method.

(7) The length of postoperative hospital stay (d) is compared between the groups using the Wilcoxon method.

(8) The incidence of intraoperative complications is compared between the groups by the  $\chi^2$  test or Fisher's exact probability method.

(9) After surgery, the incidence of complications and 30-day mortality rate are compared using the  $\chi^2$  test or the Fisher's exact tests for probability.

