## **12. Statistical analysis**

The details of statistical analysis are described in the "Statistical Analysis Plan." Before the database is locked, the statisticians discuss the plan with the principal investigators and finalize the plan according to the characteristics of the data. This plan only provides routine statistical requirements.

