## **(3) Outcome analysis**

### **Analysis of primary outcome measures**

- The DFS is calculated using the Kaplan-Meier method after the last participant has been enrolled for three years. The median DFS time and its 95% confidence interval are compared between the two groups using the log-rank test. Cox regression is used to calculate the hazard ratio and its one-sided 95% confidence interval between the two groups. According to the preset noninferiority criteria, the inferiority of the treatment to be tested compared with the control treatment is determined.

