## **7 Study endpoints**

### **7.1 Primary outcome measure**

3-year DFS rate (final calculation is done 3 years after the last participant is enrolled)

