## 8 Statistical analyses

### 8.1 Sample size estimation

The sample size was estimated using a log-rank test based on a 3-year DFS with a noninferiority margin of 10%. At the time of this trial design, a noninferiority margin of 10% was determined to be clinically acceptable. Considering distinct prognoses in patients with stage I versus II/III disease, the sample size was calculated separately. Assumptions for the 3-year DFS rate in the open surgery group were 94.3% and 75.2% for clinical stage I and II/III diseases, respectively, with 359 patients with stage I disease (laparoscopic 240, open 119), 609 patients with stage II/III disease (laparoscopic 406, open 203), and a total of 968 patients (laparoscopic 646, open 322) were required to provide an 80% power with a one-sided  $\alpha$  of 2.5%. One thousand sixty-five patients were aimed to enroll to allow for exclusions after

randomization to maintain the required statistical power. All calculations allowed for a 20% dropout. The planned and follow-up period were three years and five years, respectively.

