**Table 7. The DFS (mon) for Laparoscopic Surgery vs Open Surgery within 3 Years after Surgery (mITT)**

|                    | Laparoscopic Surgery Group | Open Surgery Group | P value |
|--------------------|-----------------------------------|---------------------------|-----------------------|
| N           | XXX                               | XXX                       | X.XXX                 |
| Censored(%) | XX(XX.X)                          | XX(XX.X)                  |                       |
| Events(%)   | XX(XX.X)                          | XX(XX.X)                  |                       |
| 25%(95%CI)  | XX.X (XX.X~XX.X)                  | XX.X (XX.X~XX.X)          |                       |
| 50%(95%CI)  | XX.X (XX.X~XX.X)                  | XX.X (XX.X~XX.X)          |                       |
| 75%(95%CI)  | XX.X (XX.X~XX.X)                  | XX.X (XX.X~XX.X)          |                       |

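### The margin is 10 points on the 3-year DFS rate at one-sided 2.5%, but the primary analysis names a log-rank test and a Cox hazard ratio with a one-sided 95% interval and no rule tying either to that margin

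*Combined protocol and SAP*

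**What the plan says.** **Endpoint.** SAP 7.1 and Protocol 8.1 give "3-year DFS rate (final calculation is done 3 years after the last participant is enrolled").

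**Margin and design.** SAP 8.1 says "The sample size was estimated using a log-rank test based on a 3-year DFS with a noninferiority margin of 10"%. Alpha is one-sided 2.5% and power 80%. "Assumptions for the 3-year DFS rate in the open surgery group were 94.3% and 75.2% for clinical stage I and II/III diseases, respectively". The strata are sized separately: "359 patients with stage I disease (laparoscopic 240, open 119), 609 patients with stage II/III disease (laparoscopic 406, open 203"), 968 in total.

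**Primary analysis.** SAP 8.3.3 and Protocol 12.2(3) plan Kaplan-Meier estimation, then: "The median DFS time and its 95% confidence interval are compared between the two groups using the log-rank test". A Cox HR with a one-sided 95% confidence interval follows. The protocol closes with "According to the preset noninferiority criteria, the inferiority of the treatment to be tested compared with the control treatment is determined". The SAP sentence is the same except that it calls the criteria prespecified. Neither document writes such criteria out for the HR, the log-rank test or a difference in rates.

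**Outputs (SAP 9).** Tables 7 and 8 give numbers of events, DFS quartiles and a P value. Table 9 gives the HR with limits and a P value. Figures 1 and 2 are Kaplan-Meier curves labelled as comparing the 3-year DFS rate, in mITT and PPS respectively.

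**Finalisation.** Protocol 12 has the statisticians and principal investigators, before database lock, "finalize the plan according to the characteristics of the data". The trial is open-label.

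**The concern.** A noninferiority conclusion needs one statistic, one confidence bound and one threshold on the same scale. Here the threshold is an absolute difference in 3-year rates, and the named statistics are something else.

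- The log-rank test as described tests equality of the two curves. A non-significant P value is not evidence of noninferiority. SAP 8.4 sets two-sided P < 0.05 as the general rule and makes no exception for the primary test.
- The HR bound has no stated value to be compared with. Turning 10 points into an HR requires a control rate, a stratum and proportional hazards, and the plan chooses none of them.
- A one-sided 95% interval tests at 5%, twice the alpha used for the design.
- The strata are sized separately, but the analysis describes a single comparison. The plan does not say whether noninferiority is claimed overall or by stage.

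At stake is the trial's main conclusion: the same data could pass or fail according to a threshold that is not written down.

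**Working it through.** **Inputs.** SAP 8.1: open-arm 3-year DFS p = 0.943 (stage I) and 0.752 (stage II/III); 240:119 and 406:203 patients; margin 10%; one-sided alpha 2.5%; power 80%; 20% dropout. Assumptions of this check: exponential DFS, proportional hazards, uniform accrual over 3 years, and analysis 3 years after last enrolment. The accrual sentence in SAP 8.1 is unclear, so the 3-year accrual is an assumption.

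**1. HR equivalent of 10 points.** HR = ln(p - 0.10) / ln(p).
- Stage I: ln(0.843)/ln(0.943) = 0.1708/0.0587 = 2.91
- Stage II/III: ln(0.652)/ln(0.752) = 0.4277/0.2850 = 1.50
- Pooled rate: (359 × 0.943 + 609 × 0.752)/968 = 0.823; ln(0.723)/ln(0.823) = 0.3246/0.1950 = 1.66

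**2. Do these reproduce the plan's sample sizes?** Events = (1.960 + 0.842)² / [(1/3)(2/3)(ln HR)²], and N = events / P(event), with no true difference.
- Stage I: 31.0 / 0.0841 = 368 (plan 359)
- Stage II/III: 214.4 / 0.3457 = 620 (plan 609)

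Both are within 3%, before dropout. Dividing by 0.80 gives 460 and 775, which do not fit. One-sided 5% with division by 0.80 gives 362 and 611, within 1%. The fit is therefore not unique, and the sponsor should state the inputs. A 10% relative margin at the first settings would give 397 and 1033, so absolute points is the reading that fits. The design implies two HR margins, and neither is written down.

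**3. What one HR threshold would allow.** Loss at 3 years = p - p^HR.

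| HR | Stage I | Stage II/III |
|---|---|---|
| 1.50 | 2.7 points | 10.0 points |
| 1.66 | 3.6 points | 13.0 points |
| 2.91 | 10.0 points | 31.6 points |

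The HR of 1.66 treats the pooled population as homogeneous. As a common HR in both stages it averages 0.371 × 3.6 + 0.629 × 13.0 = 9.5 points. The common HR that averages 10 points is 1.70 (0.371 × 3.8 + 0.629 × 13.6 = 10.0).

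**4. Medians.** Tables 7 and 8 cover 3 years. At the planning rates more than half of patients are event-free then, so no median is reached in that window whatever the survival model. Over longer follow-up, the exponential median is 3 ln 2 / (-ln p): 7.3 years in stage II/III and 35 years in stage I. Maximum follow-up at the analysis is about 3 + 3 = 6 years.

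**5. Power of a direct test of the 3-year difference.** Binomial variance, no true difference: SE² = p(1 - p)(1/n_lap + 1/n_open), power = Φ(0.10/SE - 1.960). The stratified SE uses weights 359/968 and 609/968.

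| Population | SE, full N | Power, full N | Power, 80% retained |
|---|---|---|---|
| Stage I | 0.0260 | 97% | 93% |
| Stage II/III | 0.0371 | 77% | 67% |
| Overall, pooled rate | 0.0260 | 97% | 93% |
| Overall, stage-stratified | 0.0253 | 98% | 94% |

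**The case against.** The strongest reply is that the plan needs only reading together. It starts from Kaplan-Meier estimates, ends with a reference to noninferiority criteria, and the only such criterion in the documents is 10% on 3-year DFS. Figures 1 and 2 name that rate. The planning rates were fixed in advance, so an HR margin can be recovered from them, and stage-specific HR margins would match the log-rank design. Table 9 has columns for both a lower and an upper 95% limit, which suggests a two-sided interval and hence a 2.5% bound. The median wording is repeated for OS and recurrence, and an unreached median would print as not estimable without biasing anything.

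Much of this stands. A reader might infer that the plan cannot test its hypothesis at all. The documents do not support that, because the Kaplan-Meier estimates contain what is needed. A reader might also infer that the threshold would be set after seeing the data. That does not follow: pre-trial inputs give candidate margins, and Protocol 12 places finalisation before database lock. It remains a risk, because lock is weak protection in an open-label trial.

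What does not stand is that the rule is already specified. Recovering an HR leaves a choice between 2.91, 1.50 and a pooled value. The figures are assigned no difference, interval or margin. Table 9's two limits conflict with the one-sided 95% interval in the text, and nothing settles which governs.

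**Conclusion.** The point holds as a missing and mismatched decision rule. The margin is on the 3-year rate at one-sided 2.5%. The named statistics are on other scales, the interval in the text works at 5%, and no output shows the difference, its interval or the margin.

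The size is best expressed by the candidate HR thresholds: 2.91, 1.50 and 1.66 (1.70 as a common HR). Using 1.66 would allow a 13.0-point loss in stage II/III, 3 points beyond the margin. A reader might look instead to the 31.6 points obtained by carrying the stage I HR into stage II/III. That case is artificial, since the plan sizes the stages separately and nothing suggests such a transfer.

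The conversions rest on the planning rates and proportional hazards. The comparison of medians with follow-up beyond 3 years also rests on exponential survival and 3-year accrual. The scale mismatch, the alpha mismatch and the absent rule rest on the text alone.

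**What to change.** In SAP 8.3.3 and Protocol 12.2:

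1. Define the primary test as the stage-stratified Kaplan-Meier difference in 3-year DFS, laparoscopic minus open, with Greenwood variance and stage weights stated in advance.
2. Declare noninferiority if the lower limit of the two-sided 95% confidence interval (one-sided 97.5%) is above -10 points. Replace the one-sided 95% interval.
3. State that the claim is for the overall population, with stage-specific results also reported. The power figures support this choice: stage II/III alone falls short of 80%.
4. Add a table of the 3-year rates, their difference and its interval, for mITT and PPS.
5. Make the log-rank P value and Cox HR supportive, and drop the comparison of medians.
6. Fix the rule before any outcome data by arm are tabulated.

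Stage-specific HR margins, written down with their conversion and a 97.5% bound, would also close the gap. They depend on proportional hazards and on the assumed control rates, which the direct difference avoids.

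The cost is wording in two documents and one table. No new data or patients are needed for the overall claim.

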|                               | 
6) ASA classification IV or V;
 
7) Current pregnancy or lactation:
 
 
● Women of childbearing age with a positive pregnancy test at baseline or who have not taken a pregnancy test; postmenopausal women must be at least 12 months postmenopausal
 
● Sexually active men and women (of reproductive age) who are unwilling to take contraceptive measures during the study period
 
 
8) Severe mental illness;
 
9) Inability to tolerate surgery due to severe emphysema, interstitial pneumonia, ischemic heart disease, etc.;
 
10) Continuous systemic steroid therapy within the last month;
 
11) Contraindications to laparoscopic surgery;
 
12) Patients and their family members cannot understand the conditions and objectives of this study.
                                                                                                                                                                                      |
| Sample size estimation | 
The sample size was estimated using a log-rank test based on a 3-year DFS with a noninferiority margin of 10%. At the time of this trial design, a noninferiority margin of 10% was determined to be clinically acceptable. Considering distinct prognoses in patients with stage I versus II/III disease, the sample size was calculated separately. Assumptions for the 3-year DFS rate in the open surgery group were 94.3% and 75.2% for clinical stage I and II/III, respectively, with 359 patients with stage I disease (laparoscopic 240, open 119), 609 patients with stage II/III disease (laparoscopic 406, open 203), and a total of 968 patients (laparoscopic 646, open 322) were required to provide an 80% power with a one-sided <math>\alpha</math> of 2.5%. 1065 patients were aimed to enroll to allow for exclusions after randomization to maintain the required statistical power. All calculations allowed for a 20% dropout. The planned and follow-up period were three years and five years, respectively.
 |

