#### **8.4 Statistical software and general requirements**

(1) SAS 9.4 is used for analysis (SAS Institute Inc., Cary, NC, USA).

(2) Generally, two-sided tests are used for statistical analysis, and a  $P$  value  $< 0.05$  indicates that the difference is statistically significant.

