**Table 9. Cox Regression Model Analysis of DFS (mITT)**

|               |                                      | DF | HR | 95%CIL | 95%CIU | P value |
|---------------|--------------------------------------|-----------|-----------|---------------|---------------|----------------|
| Group  | Laparoscopic Surgery vs Open Surgery | X         | X.XX      | X.XX          | X.XX          | X.XXX          |
| Center | Center 1 vs Center X                 | X         | X.XX      | X.XX          | X.XX          | X.XXX          |
|               | Center 2 vs Center X                 | X         | X.XX      | X.XX          | X.XX          | X.XXX          |
|               | Center...vs Center X                 | X         | X.XX      | X.XX          | X.XX          | X.XXX          |
| XXX    |                                      | X         | X.XX      | X.XX          | X.XX          | X.XXX          |

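### The level of the primary noninferiority test is stated inconsistently: sizing uses one-sided 2.5%, but the primary analysis names a one-sided 95% interval

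*Combined protocol and SAP*

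**What the plan says.** **Sizing.** The protocol's Summary of Study Plan, Protocol section 5 and SAP 8.1 carry the same statement: the patient numbers "were required to provide an 80% power with a one-sided" alpha of 2.5%. The calculation is "based on a 3-year DFS with a noninferiority margin of 10" percent, and the assumed rates "in the open surgery group were 94.3% and 75.2% for clinical stage I and II/III diseases, respectively".

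**Primary analysis.** Protocol 12.2 (3) and SAP 8.3.3 share one sentence: "Cox regression is used to calculate the hazard ratio and its one-sided 95% confidence interval between the two groups". In the SAP the next sentence reads: "According to the prespecified noninferiority criteria, the inferiority of the treatment to be tested compared with the control treatment is determined". The protocol's version differs only trivially. Neither gives a limit, a level or a hazard ratio margin.

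**General rule.** Protocol 12.3 and SAP 8.4: "Generally, two-sided tests are used for statistical analysis", with significance at P below 0.05.

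**Table shell.** SAP Table 9, for the Cox model of DFS, has one column for a lower 95% limit and one for an upper 95% limit. It does not say whether they are two-sided.

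**The concern.** A one-sided 95% limit corresponds to a one-sided test at 5%, and a two-sided 95% interval to one at 2.5%. The only hazard ratio interval that the primary analysis text names is the one-sided 95% interval, and it stands directly before the sentence that judges noninferiority. On the plain reading, the decision is therefore made at a level that the sizing statement does not allow.

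This is the error rate for the only primary outcome. A result between the two limits passes under one reading and fails under the other. Protocol section 12 lets the SAP be finalised before database lock in the light of the data's characteristics, so the level should be settled in the text before then.

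**Working it through.** **1. The plan's own sample size.** Inputs from SAP 8.1: control 3-year DFS p = 0.943 (stage I) and 0.752 (stage II/III), margin 0.10, allocation 646:322 (two thirds laparoscopic), power 80%, dropout 20%. SAP 7.1 puts the analysis 3 years after last enrolment. Assumptions: proportional exponential hazards and uniform accrual over 3 years. The plan's sentence on study periods is ambiguous, so the accrual time is not a stated figure.

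- Margin as a hazard ratio, ln(p − 0.10)/ln(p): 2.91 for stage I, 1.50 for stage II/III.
- Events: D = (z_α + z_β)² / [(2/3)(1/3)(ln HR)²]. At one-sided 2.5%, (1.960 + 0.842)² = 7.849 gives 31 and 215 events. At 5%, (1.645 + 0.842)² = 6.183 gives 24.4 and 168.9.
- Event probability under equal hazards, 3 + 3 years: P = 1 − (p − p²)/(−ln p) = 0.0841 and 0.3457.
- N = D/P, divided by 0.8 where dropout is allowed for.

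| Case | Stage I | Stage II/III | Total |
|---|---|---|---|
| Stated | 359 | 609 | 968 |
| 2.5%, no dropout allowance | 368 | 622 | 990 |
| 2.5%, 20% dropout | 461 | 778 | 1,239 |
| 5%, 20% dropout (events unrounded) | 362 | 611 | 973 |

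With events rounded up, the last row becomes 372 and 612 (984). With 3 years' accrual and 5 years' follow-up, 2.5% and 20% dropout give 325 and 586 (911), which 968 would cover. No single method tried, with 2.5% and 20% dropout together, gave both stage figures.

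Power of the stated N after 20% loss, 3 + 3 years: Φ(√(2D/9) × ln HR − z_α), with D = N × 0.8 × P.

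- Stage I, D = 24.2: Φ(2.475 − 1.960) = 70% at 2.5%; Φ(2.475 − 1.645) = 80% at 5%.
- Stage II/III, D = 168.4: Φ(2.483 − 1.960) = 70% at 2.5%; Φ(2.483 − 1.645) = 80% at 5%.

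**2. The level.** One-sided 95% limit: α = 1 − 0.95 = 0.050. Two-sided 95% interval: α = 0.05/2 = 0.025 in the unfavourable tail. The ratio is 0.050/0.025 = 2. A design with 80% power at 2.5% has Φ(1.960 + 0.842 − 1.645) = 87.6% power at 5%. At equal power, 2.5% needs 7.849/6.183 = 1.27 times the information.

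**3. What passes.** The margin is given in percentage points, so this illustration uses the 3-year DFS difference weighted by planned stage shares (359/968 and 609/968). The SAP does not specify that estimator.

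- SE² = Σ w² p(1 − p)(1/n_lap + 1/n_open)/0.8, with n = 240/119 and 406/203.
- Stage I: 0.943 × 0.057 × (1/240 + 1/119) = 0.000676. Stage II/III: 0.752 × 0.248 × (1/406 + 1/203) = 0.001378.
- SE = √[(0.1375 × 0.000676 + 0.3958 × 0.001378)/0.8] = 0.0282.
- Largest passing deficit: 0.10 − 1.960 × 0.0282 = 4.5 points at 2.5%; 0.10 − 1.645 × 0.0282 = 5.4 points at 5%.
- Stage II/III alone: SE = √(0.001378/0.8) = 0.0415, giving 1.9 and 3.2 points.

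**4. Sensitivity of the pooled limits.** With the enrolment target of 1,065 in place of 968, SE = 0.0282 × √(968/1065) = 0.0269 and the limits are 4.7 and 5.6 points. On the hazard ratio scale (3 + 3 years, 20% loss, pooled margin converted to HR 1.66) they are about 3.7 and 4.6 points. The pooled gap is about 0.9 point each time; the limits move.

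**The case against.** The strongest reply is that the plan never says the one-sided 95% limit decides. The Cox model yields the hazard ratio and its interval, and a separate sentence refers the decision to preset criteria. The only criteria stated are the 10-point margin and, in the sizing text, one-sided 2.5%. With no hazard ratio margin given, the interval cannot be set against the margin at all. On that reading the interval is descriptive and the test stays at 2.5%. This stands as far as it goes: the doubling is conditional. It does not remove the problem, because the plan then has no stated decision limit.

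A reader might also infer that Table 9 and the general rule are further contradictions. They are not. Two-sided P below 0.05 puts 2.5% in each tail, and two 95% limits read as two-sided do the same. The general rule is also expressly general, so it leaves room for exceptions.

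The sample size cuts the other way. Under the assumed 3 + 3 years, the stated N fits 5% with 20% dropout far better than 2.5% with 20% dropout. A reader might infer that 5% was intended. The documents do not show that: the accrual time is assumed, and 2.5% with no dropout allowance also comes within about 3%.

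**Conclusion.** The inconsistency is real and stands in the current text of both documents. If the named limit decides noninferiority, the type I error is 5.0% against a stated 2.5%. That figure needs no assumption beyond this reading. The pass limits of 5.4 versus 4.5 points are illustrations on the difference scale and rest on the planning rates, 646/322 patients and 20% loss.

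Two stronger readings are not supported. One is that the trial's false noninferiority rate simply is double the stated one: no written rule ties the decision to this interval. The other is that open-label conduct lets the level be chosen once the result is seen: an open label does not in itself show analysts the primary result, and the protocol has the SAP finalised before lock. The fault is an unclear rule. It should be corrected, because it governs the only primary hypothesis and the wording is cheap to change.

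**What to change.** 1. In Protocol 12.2 (3) and SAP 8.3.3, replace the one-sided 95% interval with *a two-sided 95% confidence interval (equivalently a one-sided 97.5% limit)*. This matches the alpha given in all three sizing statements. Label the Table 9 columns as two-sided 95%.
2. State that noninferiority is declared only if the unfavourable limit lies inside the margin, with both on one scale. Either compare the interval for the difference in 3-year Kaplan–Meier DFS with 10 points, or state a hazard ratio equivalent of the margin. Changing the level alone would still leave a hazard ratio interval to be compared with a percentage-point margin.
3. Recheck the 80% power at one-sided 2.5% with 20% dropout, giving the accrual and follow-up times used, and restate it if needed.

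Cost: a few sentences in each document and a table label. The downside is a stricter bound and possibly a lower stated power, about 70% per stratum under the 3 + 3-year assumption.
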